### 2.5. Data Collection and Management

Patients’ data will be collected and stored in a dedicated paper-based case report form at each participating center. Patients’ data will then be entered in pseudonymized form by each participating center in a centralized computer database on REDCap. This platform complies with the Health Insurance Portability and Accountability Act in compliance with security measures and will therefore only contain data that has already been pseudonymized. Indeed, the personal data of each patient will be de-identified and replaced by an alphanumeric ID code in an ‘association key’ document accessible exclusively to the enrolling center in a password-protected Excel file and then entered into REDCap. The alphanumeric codes will be constructed according to the following order: numeric ID of the center responsible for the case; number of the recruited patient. Similarly, the patients’ EEG raw data will be transmitted in a pseudonymized European Data Format to the coordinating center via REDCap.

Each center will be granted to review only data of their own patients and will be blinded to data entered by other centers. The completeness of the data will be checked regularly by the team of the coordinating center, who will have the possibility to review data of all participating centers. If any missing data or inconsistencies are detected by the coordinating center, the participating center in question will be encouraged to check it thoroughly. Patients’ data collected and rendered pseudonymized by the participating centers will be analyzed in aggregate by the coordinating center.

Monthly call meetings between all participating centers and the Clinical Trial Unit of the coordinating center will be planned, for ensuring the appropriateness of the patients’ enrollment, of the informed consent collection, and of data privacy management, of quality of data acquisition, and of any reported adverse events.

### 2.6. Statistical Plan

All analyses will be conducted by blinded statisticians. Frequencies (percentages) or mean ± standard deviation will be used for descriptive statistics regarding socio-demographic and clinical variables, as well as for the level of satisfaction with the experimental intervention and the occurrence of side effects.

Given that most outcomes are ordinal or exhibit skewed distributions, we will employ linear or generalized linear mixed-effects models (LMM/GLMM) with appropriate link functions. Ordinal outcomes will be analyzed using cumulative logit mixed-effects models, with random intercepts for patients and for enrolling centers. Continuous outcomes approximately normally distributed will be analyzed with LMM, while skewed continuous outcomes will be modeled with appropriate link functions (e.g., log). All models will adjust for baseline values of the outcome (ANCOVA framework) and include time (T0, T1, T2) and group (VEM, TV) as fixed effects, plus their interaction. Model formulas were defined a priori. The following is an example:logit[P(Y_ij_ ≤ k)] = β_0_ + β_1_Group_i_ + β_2_Time_j_ + β_3_Baseline_i_ + β_4_(Group_i_ × Time_j_) + u_patient(i)_ + u_center(i)_
where u_patient(i)_ and u_center(i)_ are random intercepts for patient and center, respectively.

All analyses will be performed with a two-sided significance level of 0.05. Adjustment for multiple comparisons will be made using Benjamini–Hochberg false discovery rate correction. Statistical analyses will be conducted using R (version 4.4.3; R Foundation for Statistical Computing, Vienna, Austria) or equivalent statistical software. Interim analyses are planned at half of the expected sample for safety outcomes only (i.e., AEs).

Patients violating the VEM-sABI protocol will be excluded from the VEM or TV treatment, but the last clinical observation will be considered for statistical analysis, according to an intention-to-treat approach and a Missing at Random (MAR) assumption inherent to the mixed-model framework. To explore the robustness of the results in scenarios where data may be Missing Not At Random (MNAR), we will conduct pre-specified sensitivity analyses using multiple imputation and, where appropriate, alternative approaches such as joint modeling or delta-adjusted pattern-mixture models.

Protocol violations include: ex-novo administration or change in dose of proscribed drugs (see list in Appendix B), occurrence of severe AE, transfer to acute wards due to severe medical complications, futility of the intervention (as the patient regains the ability to maintain a 90° upright position for ≥15 min without signs of hemodynamic instability on two consecutive days, combined with functional trunk and lower limb control as reflected by a score of ≥3 in the mBI sub-items “Ambulation”, i.e., constant presence of one or more assistants is required during ambulation, and ≥5 in the sub-item “Stair climbing”, i.e., the patient is able to ascend/descend but is unable to carry walking aids and needs supervision and assistance), missing two consecutive sessions or more than five total sessions or request from patients or their legal representative to withdraw from the study.

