#### Sample Size

Sample size was estimated based on information from a previous study [18] enrolling patients with MCS allocated to advanced robotic verticalization using the Erigo^®^ (Hocoma, Volketswil, Switzerland) device or traditional verticalization with a traditional tilt table. The comparison of the LCF score between the two groups after eight weeks of treatment led to an increase from 3.13 ± 1.41 to 3.60 ± 1.50 in the control group (n = 15) and from 3.60 ± 1.05 to 4.40 ± 1.06 in the experimental group (n = 15; effect size f = 0.248). For a two-sided α of 0.05 and a power of 80%, we will estimate enrolling at least 49 subjects per arm (VEM and TV). To account for a possible dropout rate of 20%, a total of 118 patients will be enrolled (59 subjects per arm).

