#### 2.3.2. Trial Protocol

After screening for inclusion/exclusion criteria, a patient is enrolled in the trial and the following demographic and anamnestic variables will be collected: age, sex, education; medical history: time post-injury (TPI), etiology, morphometry and location of brain injury by brain CT scan; pharmacological therapy affecting arousal (e.g., neurosedatives); clinical diagnosis of pDoC (i.e., VS/UWS or MCS) or of eDoC according to standardized clinical criteria [1].

Within one week from enrolment (T0), the enrolled patients will undergo clinical-functional evaluations, neurophysiological assessments and serum blood sampling at study entry as described in Table 3 for primary, secondary, and exploratory outcomes. After the entry evaluation (T0), patients will perform a total of 25 (5 per week for 5 consecutive weeks) 30 min VEM or TV sessions in the same period of the day. Both interventions (i.e., VEM and TV) are non-invasive, utilize CE-marked medical devices, and are routinely used in neurorehabilitation practice. The devices comply with the EU Medical Device Regulation (MDR 2017/745).

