## 3. Discussion

Patients with sABI are characterized by high clinical complexity, severe cognitive motor disabilities, and an increased risk of developing clinical complications [42,43,44]. An appropriate and skilled comprehensive rehabilitation intervention can significantly impact clinical outcomes and improve the quality of life of patients and their caregivers [1,2,45,46,47]. An early verticalization can promote patients’ recovery and prevent cognitive-motor disabilities and clinical sequelae [3,4,5]. The present multicenter VEM-sABI study will provide new insights into the still-debated efficacy and usability of a device considered safer for verticalization of patients with sABI because it combines robotic verticalization with lower limb mobilization [12]. The study aims to achieve several outcomes. Firstly, it is expected to enroll a large and homogeneous cohort of patients with sABI admitted to post-acute rehabilitation settings. This goal could minimize the methodological bias of the available literature on this field, which most often involved small and heterogeneous patient cohorts (e.g., chronic patients with sequelae of sABI) [5,8,12,13,14]. In addition, we planned to specifically address this topic in post-acute rehabilitation, where the likelihood of patient clinical improvements due to neuroplasticity [18] and the occurrence of clinical complications are higher [42,43,44]. Moreover, we expect that the two cohorts of patients allocated in the experimental and control arm will not differ in terms of demographic and anamnestic characteristics, to avoid biases in evaluating efficacy and usability of the two treatments. Conversely, differences in clinical characteristics and cognitive functions between patients with pDoC and those eDoC are expected. For this reason, targeted clinical and neurophysiological measures will be adopted to detect specific changes in outcome as a function of clinical diagnosis and to identify patients’ profiles with high probability to respond to both (or at least one of the two) treatments. Additionally, we expect the following study outcomes from the data analysis: (i) an improvement of cognitive levels, disability, and motor function at the end of the treatment in both arms, with a significant recovery in the VEM group, in accordance with previous studies [14]; (ii) a more consistent improvement of lower limb strength, and higher reduction in spasticity in the VEM group because of combined controlled mobilization in the VEM device; (iii) lower occurrence of side effects (e.g., orthostatic hypotension) and related dropouts in the VEM arm; (iv) higher occurrence of discontinuation of verticalization due to “treatment futility” in the eDoC patients, as they are more susceptible to early regain vertical posture and gait. A further analysis of motivations of dropouts will identify clinical profiles of patients who could better match the robotic (VEM) or the traditional tilt table treatment (TV); (v) a reduction in clinical complications occurrence in both groups, based on the potential impact of verticalization on patients overall clinical stabilization [3,4]. Because most participating centers are not familiar with this robotic technology in rehabilitation of patients with sABI, we expect to see higher therapist’s compliance for traditional tilt table (i.e., higher SUS score), especially in the early stages of the study. A preliminary structured 3-day training provided by the robotic device manufacturer, on the appropriate use of the robotic device, including real-life testing on at least two different patients, will be performed to avoid potential challenges and ensure the homogeneity in the device use. To ensure ongoing protocol fidelity and inter-site consistency, we implemented the following measures: (i) competency checklist for certification to assess each operator’s ability to manage setup, tilt procedures, stepping control, safety monitoring, and patient interaction; (ii) monitoring parameters (stepping frequency, tilt parameters, adverse events). Ongoing technical and clinical support, throughout constant availability via phone calls and monthly video-call meetings, will be further provided by the coordinator to address possible concerns. We also forecast to identify changes in neurophysiological indices (as measured by EEG) and blood-biomarkers of brain plasticity in patients who will present clinical improvements. In addition, we hope that neurophysiology and biomarkers can detect any sub-clinical (para-clinical) changes caused by the two verticalization procedures. Thus, the two outcome measures will be able to provide useful information to identify patients with a high probability of response to verticalization and help clinicians plan the most appropriate and personalized treatment in such a specific population of patients with sABI.

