Age between 18 and 75 years; sABI due to traumatic, vascular, anoxic, or mixed etiology; Stable behavioral/cognitive diagnosis on at least 4 behavioral evaluations in 1 week using the Italian version of the CRS-R in patients with pDoC, or the LCF-based cognitive assessment in patients with eDoC; Time post-injury between 28 days and 6 months [1]; Not recovered upright station; Written informed consent by the patient’s legal representative/primary caregiver.	Severe medical conditions hampering verticalization (e.g., severe hypotension or conditions realizing hemodynamic instability, end stage or severe symptomatic heart failure with reduced ejection fraction, cardiac arrhythmia of new diagnosis or arrhythmic flare, severe hepatic failure, chronic severe lower limb arterio-venous disease, sepsis/septic shock, thrombus venous embolism of new diagnosis, severe autonomic dysreflexia); Severe medical conditions hampering lower limb mobilization (e.g., fractures, heterotopic ossifications); Severe medical conditions impacting EEG activity (e.g., sub-continuous or abundant EEG epileptiform abnormalities); Severe medical conditions influencing consciousness/cognitive status, such as severe hyponatremia or hypoglycemia; Contraindications to the use of Erigo^®^Basic and/or Erigo^®^Pro (Hocoma, Volketswil, Switzerland) as per technical data sheet (see Appendix A); Presence of prohibited drugs (see Appendix B).

Abbreviations: CRS-R = Coma Recovery Scale-Revised; eDoC = emergence from Disorder of Consciousness; EEG = electroencephalography; LCF = Level of Cognitive Functioning; pDoC = prolonged Disorder of Consciousness; sABI = severe Acquired Brain Injury.

**Table 3 jcm-14-06628-t003:** Summary of primary, secondary, and exploratory outcomes and measures.

Outcome	Timing, Measure
Primary outcome: Global cognitive functioning	At T0 and T1: LCF
Secondary outcomes:	
Functional disability Spasticity of lower limbs Muscular strength of lower limbs Functional independence Usability of devices from physiotherapists Adverse events	At T0, T1 and T2: DRS At T0, T1 and at T2: MAS At T0, T1 and T2: MRC. Additional clinical observation of spontaneous or reflex movement to pain stimulation in pDoC patients At T0, T1 and T2: mBI At T1: SUS Each daily session: AER
Exploratory outcomes:	

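### The stated model uses baseline as both response and covariate, so its ANCOVA adjustment does not reach the treatment effect and its type I error depends on unstated correlations

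*Protocol article*

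**What the plan says.** Section 2.6 (Statistical Plan) sets one structure for every outcome model: "All models will adjust for baseline values of the outcome (ANCOVA framework) and include time (T0, T1, T2", with group and the Group×Time interaction as further fixed effects. It states that formulas were fixed in advance and prints an example whose fixed part contains "β_1_Group_i_ + β_2_Time_j_ + β_3_Baseline_i_ + β_4_(Group_i_ × Time_j", followed by random intercepts for patient and center. Ordinal outcomes get a cumulative logit version of this model, and approximately normal ones a linear version.

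Table 3 gives the primary outcome as "At T0 and T1: LCF"; LCF at T2 is listed as exploratory. Section 2.6 also says: "All analyses will be performed with a two-sided significance level of 0.05". The Sample Size section says: "For a two-sided α of 0.05 and a power of 80%, we will estimate enrolling at least 49 subjects per arm", on the basis of "effect size f = 0.248".

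**The concern.** Two valid ways of using a baseline measurement have been merged. In an ANCOVA, baseline is a covariate and only post-baseline values are responses. In a longitudinal model with baseline as a response, T0 is a row and no baseline covariate is used. The printed model does both, so each T0 value is partly predicted by itself.

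Two things are at stake. The precision that baseline adjustment should bring may be lost from the treatment effect although the text claims it. And the self-predicted T0 rows may distort the variance estimates, so that the test does not hold the stated 5%. The wording covers all models, so the problem extends from LCF to DRS, MAS, MRC and mBI.

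**Working it through.** **Inputs.** From the article: two-sided α 0.05, power 80%, f = 0.248, 49 per arm (N = 98), 118 in total, 1:1 allocation, and the model in Section 2.6. The within-patient correlation ρ is not given, so a range is assumed.

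**Reproducing the plan's figure.** Take the between-group test of a repeated-measures ANOVA with m = 2 visits and ρ = 0.5 (neither stated). Then λ = f²·N·m/[1+(m−1)ρ] = 0.248² × 98 × 2/1.5 = 8.04, and the noncentral F gives power 80.1%. So 49 per arm is reproduced, and 98 × 1.2 ≈ 118. This calculation concerns a group difference averaged over the visits, not Group×T1.

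**Step 1: the adjustment cancels.** In the linear model, the Group×T1 coefficient is the between-arm difference in (T1 − T0). The term β3·Baseline is the same in a patient's T0 and T1 rows, so it subtracts out. With complete data the estimate equals the raw change-score difference; fitted models confirmed this to machine precision.

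**Step 2: the cost in precision.** With unit variance at each visit, the change-score variance is 2(1−ρ) and the ANCOVA residual variance is 1−ρ². The ratio is 2(1−ρ)/(1−ρ²) = 2/(1+ρ).

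| ρ | variance ratio | power, model as written | power, ANCOVA |
|---|---|---|---|
| 0.3 | 1.54 | 61.1% | 72.0% |
| 0.5 | 1.33 | 73.2% | 80.3% |
| 0.7 | 1.18 | 90.0% | 92.5% |

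Power is simulated for the linear model with two visits, N = 98 and a true effect of 0.5 SD. The middle column is flattered by the inflated error shown next. At ρ = 0.5, the same change-score comparison without the covariate, which holds about 5%, has power 68.7%.

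**Step 3: type I error with T0 and T1 only (the primary LCF visits), linear model.** Given baseline, the between-patient mean square has expectation 2 × (1−ρ²)/4 = (1−ρ²)/2. The within-patient mean square has expectation 2(1−ρ)/2 = 1−ρ. Their ratio, (1+ρ)/2, is below 1 for every ρ < 1, so the patient variance tends to be estimated as zero (90–100% of simulated runs). The two mean squares are then pooled with nearly equal degrees of freedom (95 and 96). This gives a residual variance of about (1−ρ)(3+ρ)/4 where 1−ρ is needed. The standard error is too small by the factor √[(3+ρ)/4], and the real error is about 2Φ(−1.96·√[(3+ρ)/4]).

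| ρ | standard-error factor | approximate error | simulated (N = 98 and 118) |
|---|---|---|---|
| 0.3 | 0.908 | 7.5% | 7.3–7.6% |
| 0.5 | 0.935 | 6.7% | 6.4–6.8% |
| 0.7 | 0.962 | 5.9% | 5.8–6.1% |
| 0.8 | 0.975 | 5.6% | 5.5–5.7% |
| 0.9 | 0.987 | 5.3% | 5.2–5.3% |

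**Step 4: cumulative logit model.** Simulated with N = 98, LCF levels 2–8, 2,000 runs and no center effect (Monte Carlo standard error about 0.5 points). At latent ρ of 0.5, 0.7 and 0.85, Group×T1 rejects in 8.9%, 6.5% and 3.4% with two visits, and in 6.1%, 5.4% and 4.0% with three.

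**Step 5: linear model with three visits.** Equal correlations give 4.9–5.2%. Unequal correlations (T0–T1/T0–T2/T1–T2) give 6.7% (0.6/0.5/0.85), 8.0% (0.5/0.5/0.8), 5.1% (0.8/0.7/0.9) and 2.8% (0.7/0.49/0.7). In these unequal cases, dropping the baseline covariate gives the same figures. The departure there comes from a random intercept, which implies equal correlations, combined with T0 as a row.

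**Step 6: after the fix.** With T0 out of the response and baseline as covariate, error is 4.8–5.2% in the linear simulations and 4.5–5.8% in the cumulative logit ones.

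**The case against.** The strongest reply is that this is a loosely worded sentence with limited consequences. A change-score comparison in a randomised trial is unbiased. The formula is offered as an example and is schematic, and the loss of precision shrinks as ρ rises. All of that stands. But the sentence before the formula applies to all models and says the same thing, so the double use of baseline is not a slip in the example alone.

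A reader might infer more than the article supports:

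- **That the test is generally anti-conservative.** It is not. Error is close to 5% with three equally correlated visits, and falls below 5% in the cumulative logit model at high correlation and in one three-visit linear pattern. Nor does the covariate explain the unequal-correlation results with three visits.
- **That β1 is a treatment effect fixed at zero.** In the linear model β1 equals (1−β3) times the chance baseline difference, which is small but not zero. It never rejected in the cumulative logit simulations, but the article does not name it as the test.
- **That Time is a linear trend because it has one coefficient.** The levels are listed in the same way as the two groups, which is factor notation. With categorical time, Group×T1 does address the T1 question in Table 3.
- **That the model is wrong for omitting diagnosis, etiology and time post-injury.** Adjusting for these is optional and separate from this defect.

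**Conclusion.** The model is wrong as written: it calls itself ANCOVA, but its treatment effect at T1 is not baseline-adjusted. This is exact for the linear model with complete data and approximate for the cumulative logit model that applies to LCF.

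In the linear case the variance is about 18–54% larger than under ANCOVA for ρ between 0.7 and 0.3. At ρ = 0.5 and a 0.5 SD effect, about 7 points of power are lost (73.2% against 80.3%), in a trial planned at 80%.

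Error control is uncertain rather than uniformly poor: about 5–9% in most two-visit settings (3.4% in the logit model at latent ρ 0.85) and about 3–8% with three visits. Section 2.6 lists three time levels while the primary outcome has two, so the article does not settle which case applies. All these sizes rest on assumed correlations and complete data.

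**What to change.** Rewrite the model sentence and example formula in Section 2.6 in one of two ways:

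1. Remove T0 from the response. Model T1 and T2 (or T1 alone for the primary analysis) with baseline as covariate, visit as a categorical factor, Group×visit, and the center intercept, plus the patient intercept when both visits are used.
2. Keep T0 as a response, drop the baseline covariate, constrain the arms to a common T0 mean, and use a covariance structure that allows unequal correlations between visits.

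In either case, name the VEM–TV contrast in LCF at T1 as the primary test, and use the same structure for DRS, MAS, MRC and mBI.

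The cost is one paragraph and one formula, changed before unblinding. No further data, visits or patients are needed.

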In addition, we defined a graded framework for AE seriousness and relatedness to guide session management:-Mild AE: No session suspension required. Symptoms are transient and resolve without intervention (e.g., mild and temporary facial pallor without changes in vital signs);-Moderate AE: Interruption of a single session is required. Symptoms resolve within the same day (e.g., oxygen desaturation resolving after endotracheal suctioning);-Severe AE: Permanent discontinuation of treatment is considered in case of repeated or persistent AE unresponsive to intervention (e.g., hypotension not responding to reduction in tilt angle), or based on medical judgment prioritizing patient safety.

AEs will be managed according to the 90/385/EEC and 93/42/EEC regulations.

A concomitant usual care and rehabilitation interventions will continue without restriction for both arms. Regardless of allocation to the VEM or TV group, all patients will carry out the comprehensive rehabilitation program as designed by the participating center for the entire study period. The usual rehabilitation program consists of alternating bed positioning, passive limb mobilization, cognitive training, activities to facilitate recovery of consciousness (e.g., multisensorial stimulation), speech, and swallowing therapy. During VEM in sABI study, clinicians will be asked to exercise caution when prescribing “prohibited” (i.e., not permitted under the study protocol) and “proscribed” medications (i.e., permitted but requiring careful documentation and, when necessary, adjustment in timing or dosage). These medications may compromise safety (prohibited agents associated with orthostatic hypotension), and affect the interpretability of outcomes by influencing cognition, attention, arousal, or consciousness (proscribed medications) [21,22]. A list of contra-indicated medications and/or cautions is reported in the Appendix B. Information on pharmacological treatments will be collected at baseline and at all follow-up time points.

At the end of the fifth week of treatment (T1), and after 1 month from T1 (T2) a clinical–functional and neurophysiological evaluation will be performed. A serum blood sample will be collected at T2 (see Table 3).

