### 2.4. Outcome Measures

Almost all measures will be collected at study entry (T0) and at T1 and T2 to evaluate the (possible) changes in the two follow-ups with respect to T0. Primary, secondary, and exploratory outcomes and related measures are summarized in Table 3.

The clinical–functional evaluation includes the following:-The Level of Cognitive Functioning (LCF) [24,25], an observer-rated scale (from coma to purposeful appropriate behavior) divided into eight levels that describe the patterns or stages of recovery typically seen after a brain injury.-The Coma Recovery Scale-Revised (CRS-R) [23,26] is an observer-rated tool designed to assess patients with disorders of consciousness. It evaluates auditory, visual, motor, oromotor/verbal, communication, and arousal functions to help differentiate between vegetative state, minimally conscious state, and emergence from these conditions.-The Disability Rating Scale (DRS) [27], an observer-rated, 30-point continuous scale that provides quantitative information to document the progress of patients with severe brain injury from coma to community reintegration. It evaluates 8 areas of functioning, organized into 4 categories: (1) consciousness (eye opening, verbal response, motor response); (2) cognitive ability (feeding, toileting, grooming); (3) dependence on others; (4) employability. Each area of functioning is rated on a scale of 0 to either 3, 4, or 5 (maximum score = 30-death, minimum score = 0-person without disability) with the highest scores representing the higher level of disability.-The Modified Ashworth Scale (MAS) [28], an observer-rated scale used to measure muscle spasticity by assessing resistance during passive soft-tissue stretching. Scores range from 0 (no increase in muscle tone) to 4 (rigid in flexion or extension).-The Medical Research Council (MRC) scale [29], an observer-rated scale for assessing muscle strength, scoring from 0 (no contraction) to 5 (normal strength) in specific muscle groups.-The Fondazione Don Gnocchi Clinical Complication Scale (FDG-CCS) [30], an observer-rated tool for recording and grading clinical complications during rehabilitation of patients with sABI, covering medical, nursing, and functional events to support patient monitoring and care planning.-The modified Barthel Index (mBI) [31], an observer-rated continuous scale for evaluation of ability to perform autonomously personal activities of daily living. It measures physical disability across 10 categories that are scored from 0 to either 5, 10, or 15 (maximum score = 100-independence, minimum score = 0-complete dependence) with the highest scores representing the higher level of independence.-The System Usability Scale (SUS) [32] is a simple, ten-item 5-point Likert scale giving a global view of subjective assessments of usability, including effectiveness, efficiency, and satisfaction of a device. Higher scores correspond to higher usability.-The Nociception Coma Scale–Revised (NCS-R) [33], an observer-rated tool to assess pain-related behaviors in patients with disorders of consciousness. It evaluates motor, verbal, and facial responses to noxious stimulation, with higher scores indicating stronger nociceptive responses. -The Agitated Behaviour Scale (ABS) [34], an observer-rated scale measuring the nature and extent of agitation during recovery from brain injury. It assesses behavioral, emotional, and cognitive components, with higher scores indicating greater agitation severity.

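### The last-observation rule for patients taken off treatment reads as carry-forward; if so, those stopped before T1 normally score no LCF change, which can bias the primary contrast either way

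*Protocol article*

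**What the plan says.** Section 2.6 states that "Patients violating the VEM-sABI protocol will be excluded from the VEM or TV treatment", and that for these patients "the last clinical observation will be considered for statistical analysis, according to an intention-to-treat approach and a Missing at Random (MAR) assumption". The sentence goes on to attribute the MAR assumption to the mixed model.

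The violations listed at the end of Section 2.6 cover opposite clinical courses. One is "futility of the intervention (as the patient regains the ability to maintain a 90° upright position for ≥15 min", combined with minimum scores on two Barthel sub-items. Others are "occurrence of severe AE, transfer to acute wards due to severe medical complications". Changes in proscribed drugs, missed sessions and withdrawal from the study are on the same list.

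On timing, Section 2.4 says "Almost all measures will be collected at study entry (T0) and at T1 and T2". Table 3 fixes the primary outcome as "At T0 and T1: LCF", and Table 1 has no LCF entry in weeks 1 to 5. T1 falls at the end of the fifth treatment week (Section 2.3.2). No assessment at the time of stopping is described.

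The Discussion expects improvement by end of treatment in both arms, and "lower occurrence of side effects (e.g., orthostatic hypotension) and related dropouts in the VEM arm".

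For missing data, Section 2.6 also plans sensitivity analyses: multiple imputation and, where judged appropriate, joint models or delta-adjusted pattern-mixture models.

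**The concern.** A mixed model under MAR uses each observed value at its own visit and needs no substitute for a missing one. Putting the last observation in place of a later visit is single imputation, and it rests on a different assumption: that the patient would not have changed. The sentence can therefore be taken to specify two analyses of the primary outcome that do not agree.

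The schedule makes this matter. If a value is carried forward, someone stopped in weeks 1 to 5 normally has only the T0 score to carry, so the LCF change is zero by construction. The protocol itself expects patients to improve, and it expects adverse-event dropout to differ between arms. A rule that sets stopped patients to zero then moves the arm contrast by an amount set by who stops, in which arm and why, rather than by the treatment alone.

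**Working it through.** **The plan's own figure.** Section 2.2 (Sample Size) gives 49 per arm, inflated for 20% dropout to 59. A between-group test in a two-visit repeated-measures ANOVA with f = 0.248, α = 0.05, power 80% and within-patient correlation 0.5 (assumed; not stated) gives 49. The inflation is 49 × 1.2 = 58.8, so 59 per arm and 118 in total. The figure reproduces. The 20% is used below only as the plan's own dropout level.

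**Inputs.** LCF gains from the same section:
- VEM: 4.40 − 3.60 = 0.80
- TV: 3.60 − 3.13 = 0.47
- Difference: 0.33
- For a null case, both arms are given the midpoint, (0.80 + 0.47)/2 = 0.635.

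**Formula if T0 is carried forward.** The expected arm mean change is g − p × h. Here g is the true mean gain, p the fraction stopped before T1, and h the true T1 gain of those stopped. If stopping is unrelated to outcome, h = g and the mean is g(1 − p). All stop rates below except the 20% are assumptions.

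*Stopped patients would have gained the arm average:*
- 20% in both arms: 0.80 × 0.80 − 0.47 × 0.80 = 0.640 − 0.376 = 0.264, a loss of 20%.
- 10% VEM, 30% TV: 0.80 × 0.90 − 0.47 × 0.70 = 0.720 − 0.329 = 0.391.
- 30% VEM, 10% TV: 0.80 × 0.70 − 0.47 × 0.90 = 0.560 − 0.423 = 0.137.
- No true effect, 10% VEM, 25% TV: 0.635 × 0.90 − 0.635 × 0.75 = 0.5715 − 0.4763 = +0.095, which is 29% of 0.33.
- No true effect, 10% VEM, 30% TV: 0.635 × 0.20 = +0.127. In a simulation of baseline-adjusted ANCOVA (59 per arm, 3,000 runs, SD of change 1.0 assumed), two-sided rejection was 11.8%, against 5.3% with no stops.

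*Stopped patients differ from the arm average:*
- Futility stops 10% VEM, 5% TV, with h = 2 levels: (0.80 − 0.20) − (0.47 − 0.10) = 0.23. With h = 1: (0.80 − 0.10) − (0.47 − 0.05) = 0.28. With equal rates and equal h, the difference stays 0.33.
- No true effect, adverse-event stops 5% VEM, 15% TV, with h = −1: (0.635 + 0.05) − (0.635 + 0.15) = −0.10. Here the rule hides deterioration and favours TV.

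The sign therefore depends on the mix of reasons and on how stopped patients would have fared, not only on which arm loses more.

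**Limits.** The planning gains come from minimally conscious patients over eight weeks, while this trial treats a mixed population for five. Mean-change arithmetic is also not the planned cumulative logit model. The results show mechanism and order of size; they are not forecasts.

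**The case against.** The strongest reply is that the protocol never says a value is carried forward or imputed. By tying MAR to the mixed model, the sentence can be read as saying that violators stay in the analysis with whatever was observed up to exit. Time in the model includes T0, so a patient with only T0 can contribute without an invented T1 value. Removal is expressly from treatment, not from assessment, and if T1 is still measured in everyone the problem disappears. This stands as far as it goes: the wording is ambiguous, and the bias must be stated as conditional. It does not settle the matter. A last-observation rule has little purpose if T1 is always obtained, and the Discussion speaks of side-effect exits as dropouts. If removed patients simply have no T1 value, MAR is doubtful, because the triggers (adverse events, Barthel scores, drug changes) are absent from the example model.

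A second reply is that T0 need not be the last LCF available. Section 2.2 foresees patients reaching a higher level during treatment, and the futility criterion needs Barthel scores in weeks for which Table 1 schedules none. Off-schedule ratings are therefore plausible, hence *normally* rather than *always*. Such a rating would still reflect less than five weeks of recovery and is not the T1 endpoint.

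A reader might also infer that futility stops are the best cognitive recoverers, so that VEM successes are scored as failures. The document does not support this. The criterion is motor, no LCF gain is attached to it, and a two-level gain is impossible for anyone entering at level 7 or 8 of the eight-level scale. The Discussion expects these stops in eDoC patients, not more of them in VEM. Nor does anything show that patients who miss sessions have the worst courses.

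Finally, the planned sensitivity analyses help but leave the primary estimate unchanged. Multiple imputation without a shift is itself a MAR method, and the delta-adjusted model is only conditional.

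**Conclusion.** The point holds in conditional form. Section 2.6 states a rule for removed patients whose plain reading is carry-forward and which does not sit with the MAR mixed model beside it. If a value is carried forward, the visit schedule means that most patients stopped before T1 score no LCF change, and the primary contrast can be biased in either direction. At the plan's own 20% dropout, equal and non-informative, the 0.33 difference becomes 0.264. With no true effect and an assumed 25% against 10% of adverse-event stops, a false +0.095 in favour of VEM arises if those patients would have gained the average; the sign can reverse if they would have declined. With no true effect and identical exits in both arms there is no bias, but the Discussion expects adverse-event exits to be unequal.

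It would go too far to say that carry-forward is certainly planned, or that the bias has a known direction or size. The text admits another reading and gives no exit rates by arm. The correction is needed on either reading, and while follow-up is still possible, because T1 scores not collected cannot be recovered later.

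**What to change.** In Section 2.6:
- Delete the last-observation rule.
- State that patients whose sessions stop for any listed reason are still assessed on LCF and the other scales at the T1 and T2 visits already scheduled, unless they withdraw consent to follow-up.
- State that all observed values are analysed by allocated arm in the mixed model, with no value carried forward.
- Make the delta-adjusted pattern-mixture analysis, already named, a firm MNAR check, with deltas set by stopping reason. Describe unshifted multiple imputation as a MAR analysis.

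The reasons for stopping sessions need not change for this; only their effect on outcome collection does. The cost is a change of wording, no new procedure, and some effort to trace discharged or transferred patients and have them rated by blinded assessors, which will not always succeed on acute wards.
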